### 2.6. Baseline and follow-up assessments

Pupils and teachers will complete separate baseline questionnaires, and two follow-up questionnaires spaced at 2- and 7- months post-intervention. By comparing baseline and follow-up questionnaires between the intervention schools and the control school, we will be able to assess whether the intervention “Stop sexual harassment” is successful in reducing sexual and gendered harassment victimisation and perpetration among pupils. See Table 3 for a timeline of the intervention and the assessments, and Figure 1 for a flowchart of the participation rate. The primary outcomes variable consists of instruments that measure sexual harassment (28, 42) and harassment due to gender non-conformity, sexual harassment and homophobic behaviour (43, 44). For a description of primary, secondary and mediator variables, see Tables 4–6.

**Table 3 T3:** Timeline of the intervention and the assessments.

	**Wave 1**	**Wave 2**
Baseline Assessment (T1)	May–June 2021	May–June 2022
Randomisation	June 2021	June 2022
Training of teachers	August 2021	August 2022
Implementation of “Stop Sexual Harassment”	August 2021–November 2021	August 2022–November 2022
Focus group interviews		December 2022
Short term follow-up (T2)	January- March 2021 (Delay due to the COVID-19 Pandemic)	January 2023
Long term follow-up (T3)	June 2022	June 2023

**Table 4 T4:** Primary outcome variables.

	**Measure**	**Source of measure**	**Data source**
Sexual harassment *victimisation*	The AAUW sexual harassment survey (13 items)	AAUW (42); Hill and Kearl (28)	Pupils
Harassment *victimisation* due to gender non-conformity	Modified version of the Harassment perceived as occurring due to gender non-conformity (4 items)	Based on Martin-Storey and August (43)	Pupils
Harassment *victimisation* due to sexual orientation	Modified version of the Harassment perceived as occurring due to sexual minority status (4 items)	Based on Martin-Storey and August (43)	Pupils
Sexual harassment *perpetration*	The AAUW sexual harassment survey (13 items)	AAUW (42); Hill and Kearl (28)	Pupils
Harassment *perpetration* due to gender non-conformity	Modified version of the Harassment perceived as occurring due to gender non-conformity (4 items)	Based on Martin-Storey and August (43)	Pupils
Harassment *perpetration* due to sexual orientation	Modified version of the Harassment perceived as occurring due to sexual minority status (4 items)	Based on Martin-Storey and August (43)	Pupils
Homophobic behaviour	Homophobic behaviour (5 items)	Paul Poteat et al. (44)	Pupils
Sexual and gendered harassment perpetration (GASH)	Self-constructed global scale measuring: verbal sexual harassment, physical sexual harassment, sexual rumour, homophobic harassment, harassment due to gender non-conformity (6 items)		Pupils

**Table 5 T5:** Secondary outcome variables.

	**Measure**	**Source of measure**	**Data source**
Depressive symptoms	Short Moods and Feelings Questionnaire (13 items)	Angold et al. (45); Larson et al. (46); Lundervold et al. (47).	Pupils
Anxiety symptoms	Screen for Child Anxiety Related Emotional Disorders- short form (5 items)	Birmaher et al. (48); Birmaher et al. (49).	Pupils
Reactions to pupils being exposed to sexual harassment	Reactions questions based on the AAUW sexual harassment survey (26 items)	Based on AAUW (42); Hill and Kearl (28)	Teachers
Reactions to pupils being exposed to harassment due to gender non-conformity	Reactions questions based on Harassment perceived as occurring due to gender non-conformity (8 items)	Based on Martin-Storey and August (43)	Teachers
Reactions to pupils being exposed to harassment due to sexual orientation	Reactions questions based on Harassment perceived as occurring due to sexual minority status (8 items)	Based on Martin-Storey and August (43)	Teachers
Reactions to pupils being exposed homophobic harassment	Reactions questions based on Homophobic behaviour (10 items)	Based on Paul Poteat et al. (44)	Teachers
Reactions to GASH perpetration among pupils	Theory of planned behaviour scale measuring teachers reactions towards sexual and gendered harassment perpetration among pupils (10 items)	Based on Fishbein and Ajzen, 2010 (50)	Teachers
Attitudes towards reacting to GASH perpetration among pupils	Theory of planned behaviour scale measuring attitude towards reacting to GASH perpetration among pupils (6 items)	Based on Fishbein and Ajzen, 2010 (50)	Teachers
Intention to react to GASH perpetration among pupils	Theory of planned behaviour scale measuring intention to react to GASH perpetration among pupils (6 items)	Based on Fishbein and Ajzen (50)	Teachers
Subjective norms regarding reacting to GASH perpetration among pupils	Theory of planned behaviour scale measuring subjective norms regarding reacting to GASH perpetration among pupils (6 items)	Based on Fishbein and Ajzen, 2010 (50)	Teachers
Perceived behavioural control regarding reacting to GASH perpetration among pupils	Theory of planned behaviour scale measuring behavioural control regarding reacting to GASH perpetration among pupils (6 items)	Based on Fishbein and Ajzen (50)	Teachers

**Table 6 T6:** Mediator variables.

	**Measure**	**Source of measure**	**Data source**
Attitudes towards gendered and sexual harassment (GASH)	Theory of planned behaviour scale measuring attitudes towards GASH (6 questions)	Based on Fishbein and Ajzen (50)	Pupils
Reporting GASH to teachers	Theory of planned behaviour scale measuring having told a teacher when a co-student was exposed to GASH (6 questions)	Based on Fishbein and Ajzen (50)	Pupils
Intention to report GASH to teachers	Theory of planned behaviour scale measuring intention to tell a teacher if a co-student is exposed to GASH (6 questions)	Based on Fishbein and Ajzen (50)	Pupils
Bystander GASH behaviour	Theory of planned behaviour scale measuring prosocial bystander behaviour when a co student was exposed to GASH (6 questions)	Based on Fishbein and Ajzen (50)	Pupils
Intention to perform bystander GASH behaviour	Theory of planned behaviour scale measuring intention to perform prosocial bystander behaviour if a co-student is to be exposed to GASH (6 questions)	Based on Fishbein and Ajzen (50)	Pupils
Attitudes towards performing bystander GASH behaviour	Theory of planned behaviour scale measuring attitudes towards performing prosocial bystander behaviour if a co-student is exposed to GASH (6 questions)	Based on Fishbein and Ajzen (50)	Pupils
Subjective norms regarding performing bystander GASH behaviour	Theory of planned behaviour scale measuring subjective norms regarding performing prosocial bystander behaviour if a co-student is exposed to GASH (6 questions)	Based on Fishbein and Ajzen (50)	Pupils
Perceived behaviour control regarding performing bystander GASH behaviour	Theory of planned behaviour scale measuring perceived behaviour control regarding performing prosocial bystander behaviour if a co-student is exposed to GASH (6 questions)	Based on Fishbein and Ajzen (50)	Pupils
Reactions to sexual harassment victimisation	Reactions questions based on AAUW sexual harassment survey (26 items)	Based on AAUW (42); Hill and Kearl (28)	Pupils
Reactions to harassment victimisation due to gender nonconformity	Reactions questions based on the Harassment perceived as occurring due to gender nonconformity (8 items)	Based on Martin-Storey and August (43)	Pupils
Reactions to harassment victimisation due to sexual orientation	Reactions questions based on Harassment perceived as occurring due to sexual minority status (8 items)	Based on Martin-Storey and August (43)	Pupils
Bullying victimisation and perpetration	Bullying victimisation, and perpetration, with and without sexual content (4 item)	Solberg and Olweus (51); Olweus et al. (36)	Pupils
The Bergen Questionnaire on Antisocial Behaviour	(9 items)	Based on Bendixen and Olweus, 1999 (52); Bendixen et al. (53)	Pupils

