**Methods:**

In this study the effectiveness of “Stop Sexual Harassment” is evaluated *via* a cluster randomised controlled trial among pupils and teachers at 38 secondary schools. Schools were randomised into intervention and control groups. Primary outcomes are sexual and gendered harassment victimisation and perpetration, which will be assessed by the administration of questionnaires to pupils and teachers at baseline, and 2-, and 7-months follow-up. A process evaluation of the intervention implementation will be conducted through focus group interviews with pupils and teachers to gain insight about their experiences with the program components and implementation of the intervention.

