### 2.5. Randomisation procedure

The intervention “Stop Sexual Harassment” is a whole school approach that involves all members of the school community. Comparisons must thus be at the school and not the individual level and schools were chosen as the cluster of randomisation. Schools were randomised into intervention and control schools by an independent professional [i.e., external statistician working at Services for sensitive data (TSD)]. The randomisation was stratified based on number of participating classes within each school with a 1:1 allocation. All schools were paired based on similarity in size of participating classes and whether they were public or private schools. Syntax (in stata) was used to randomly assign one school in each pair to the intervention group for both wave 1 and wave 2. The remaining school of each pair was assigned to the wait-list control group. Schools were informed about their allocation after completing baseline questionnaires.

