### 2.7. Data collection procedures

Questionnaires to pupils and teachers are administered electronically, distributed by a survey tool (Nettskjema; https://nettskjema.no/?lang=en). For pupils, data will be collected during school hours. Pupils who are quarantined or home-schooled during the COVID-19 restrictions, or not present at school for other reasons, when the questionnaires are administered, may complete these at home. It takes about 30 min to complete the pupil questionnaire and about 20 min to complete the teacher questionnaire.

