### 2.8. Data analysis

Descriptive statistical analyses and frequency tables will be used for comparisons between intervention and control group. Multilevel modelling will be used to assess the impact of the intervention on the primary and secondary outcome variables. Potential subgroup differences (e.g., gender) will be analysed by including interaction effects. The psychometric qualities of the outcome variables will be assessed by descriptive statistics (e.g., floor/ceiling effects), correlation analyses and exploratory and confirmatory factor analysis. Missing data will be handled by multiple imputation and full information maximum likelihood.

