### 3.2. Recruitment of participants

All principals in the intervention group were invited by e-mail or phone to participate in a process evaluation of the intervention. Three schools from wave 1 volunteered for focus group interviews. However, the interviews were cancelled due to national COVID-19 imposed regulations restricting pupils to meet between classes and a high number of pupils and teachers being absent from school. Online meetings were not considered, as participation would require individual rooms for participants at each class. It was decided to postpone the focus group interviews to wave 2. For wave 2, three schools will be invited to participate in the focus group interviews. At each school, there will be one interview with six pupils, and one interview with six teachers. The recruitment of teachers and pupils to focus group interviews will be conducted by the principals, with the instruction to balance the informant group with regard to gender and age. Prior to participation in the interviews, parents, pupils and teachers will be given information about the process study and asked to sign consent/assent forms.

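### Table 3 dates the wave 1 short-term follow-up before its own baseline; with the year corrected, it falls about 2 to 4 months after delivery, not the stated 2

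*Protocol article*

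**What the plan says.** The abstract gives one schedule for all schools: "questionnaires to pupils and teachers at baseline, and 2-, and 7-months follow-up". Section 2.6 repeats it as "two follow-up questionnaires spaced at 2- and 7- months post-intervention". Neither place distinguishes the two waves.

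Table 3, in the same section, gives the calendar by wave. For wave 1:

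- baseline: May–June 2021
- randomisation: June 2021
- delivery: "August 2021–November 2021"
- T2: "January- March 2021 (Delay due to the COVID-19 Pandemic"
- T3: June 2022

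For wave 2 the same steps run from May–June 2022, with delivery from August to November 2022, T2 in January 2023 and T3 in June 2023.

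Section 2.5 describes paired schools and code used to "randomly assign one school in each pair to the intervention group for both wave 1 and wave 2". On analysis, section 2.8 says: "Multilevel modelling will be used to assess the impact of the intervention on the primary and secondary outcome variables". It does not mention wave.

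**The concern.** There are two faults in the schedule, and the first hides the second. The printed year puts wave 1 T2 before the baseline it is meant to follow. Once the year is put right, the three-month window no longer fits the 2-month label used for the whole trial.

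T2 is one of only two assessments after baseline, and the primary outcomes are measured at it. A short-term result reported as the effect at 2 months would in part describe schools surveyed up to 4 months after the lessons ended. The reader would have no way of knowing this from the abstract or the text. The interval between the two follow-ups also differs between waves.

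**Working it through.** **Inputs.** All dates are from Table 3; the stated follow-up times are from the abstract and section 2.6. Only months are given, so the main count is in calendar months from November, the last month of delivery. A count in days (divided by 30.4375) shows how far the result depends on the day chosen.

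**Step 1: reproduce the stated figures where they hold.**

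- Wave 2 T2: November 2022 to January 2023 = 2 months. Matches.
- Wave 2 T3: November 2022 to June 2023 = 7 months. Matches.
- Wave 1 T3: November 2021 to June 2022 = 7 months. Matches.

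The calendar-month count from November is therefore the one that yields the plan's own 2 and 7 months.

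**Step 2: wave 1 T2 as printed.** The window ends on 31 March 2021 at the latest. Baseline starts on 1 May 2021 at the earliest, so T2 would end about 1 month before baseline begins. It would lie about 8 to 11 months before the end of delivery (31 March or 1 January 2021, against 30 November 2021). This cannot be right.

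**Step 3: which year fits.** T2 must fall after delivery (to November 2021) and before T3 (June 2022). The only January–March in that interval is in 2022.

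**Step 4: wave 1 T2 read as 2022.**

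- November 2021 to January 2022 = 2 months
- November 2021 to February 2022 = 3 months
- November 2021 to March 2022 = 4 months

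The range is 2 to 4 months, against a stated 2.

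**Step 5: gap from T2 to T3.**

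- Wave 1: March to June = 3 months; January to June = 5 months. Range 3 to 5.
- Wave 2: January to June = 5 months.

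**Step 6: sensitivity to the day chosen.**

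| Quantity | Wave 1 (T2 read as 2022) | Wave 2 |
|---|---|---|
| T2 counted from 30 November | 1.0 to 4.0 months | 1.0 to 2.0 months |
| T2 to T3, extreme days | 2.0 to 5.9 months | 4.0 to 5.9 months |

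Counted from 1 November, wave 1 T2 is 2.0 to 4.9 months. The exact limits move, but on every count the wave 1 window extends well past that of wave 2.

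**What cannot be computed.** The number of schools per wave is not in the text (the flow diagram is not shown), and neither is the spread of wave 1 schools over January to March. The share of T2 data that falls outside 2 months is therefore unknown.

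**The case against.** The strongest reply is that this is a slip in one table cell. Table 3 openly gives the longer window and the reason for it, 2 months is a nominal label, and the handling of wave may stand in an analysis plan that is not shown. Part of this holds. The absence of a wave term from section 2.8 is not itself a fault, and no pooled T2 analysis is written out; pooling is only the natural reading of one trial with one set of time points. But an unseen plan does not correct a date that is impossible as printed, or a label contradicted by the table in its own section.

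A reader might also infer more than the documents support:

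- **That wave 1 T2 was collected while pupil contact was restricted, so that harassment was low in both arms.** Section 3.2 does cite "national COVID-19 imposed regulations restricting pupils to meet between classes and a high number of pupils and teachers being absent from school", but as the reason for cancelling the wave 1 focus groups, and without a date. Section 2.7 allows home completion for "Pupils who are quarantined or home-schooled during the COVID-19 restrictions", without tying it to T2. Table 3 gives the pandemic as the cause of a delay, which fits equally well with waiting until conditions eased. Section 2.3 adds that pupils spend nearly all week with the same class, so a rule on mixing between classes need not remove contact within them. Reduced contact is possible but not documented.
- **That survey month confounds the comparison of arms.** One school of each pair was randomised to each arm in both waves, and Table 3 gives both arms the same window. Nothing suggests that survey months differed by arm.
- **That a larger effect at T3 would be misread as growth.** The hypotheses in section 1.1 compare intervention with wait-list schools; none compares T2 with T3.
- **That the pooled T2 effect shrinks by a known amount.** This would need the wave split and the loss of effect in wave 1, and the documents give neither.

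**Conclusion.** The point holds as an error in the operative schedule. The wave 1 T2 year is wrong as printed. Read as 2022, the only year that fits the sequence, T2 falls about 2 to 4 calendar months after delivery in wave 1 and 2 months after it in wave 2. The single 2-month label is wrong for wave 1, while the 7-month label is right for both waves. The consequence is a short-term estimate with a mixed time point and possible differences between waves. The documents do not show a bias between arms.

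The conclusion assumes that delivery ended in November, as Table 3 states, and that the month names in the T2 cell are right and only the year is wrong. It deserves correction because it governs what the short-term primary-outcome result can claim.

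**What to change.** 1. Correct the year of wave 1 T2 in Table 3.
2. Wherever 2 months is given (abstract, section 2.6), state T2 as about 2 to 4 months in wave 1 and 2 months in wave 2.
3. Include wave as a factor in the T2 model. Wave is fixed before randomisation, and schools were allocated in pairs in both waves, so this adjustment is safe.
4. Keep the pooled T2 estimate, described as 2 to 4 months after delivery. Beside it, report the T2 effect by wave, from an arm-by-wave term, as a supporting analysis.
5. Use the actual survey date only in a sensitivity analysis, because it arises after randomisation. Calendar date is the usable form: time since delivery has no direct meaning in wait-list schools.

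The cost is a table correction and a few lines of wording. No new data are needed, assuming that the electronic questionnaires record the completion date. The downside is that wave-specific T2 estimates are less precise than the pooled one, which is why they should support it and not replace it.

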### 2.7. Data collection procedures

Questionnaires to pupils and teachers are administered electronically, distributed by a survey tool (Nettskjema; https://nettskjema.no/?lang=en). For pupils, data will be collected during school hours. Pupils who are quarantined or home-schooled during the COVID-19 restrictions, or not present at school for other reasons, when the questionnaires are administered, may complete these at home. It takes about 30 min to complete the pupil questionnaire and about 20 min to complete the teacher questionnaire.

### 2.8. Data analysis

Descriptive statistical analyses and frequency tables will be used for comparisons between intervention and control group. Multilevel modelling will be used to assess the impact of the intervention on the primary and secondary outcome variables. Potential subgroup differences (e.g., gender) will be analysed by including interaction effects. The psychometric qualities of the outcome variables will be assessed by descriptive statistics (e.g., floor/ceiling effects), correlation analyses and exploratory and confirmatory factor analysis. Missing data will be handled by multiple imputation and full information maximum likelihood.

### 2.9. Data protection

The questionnaires will be administered electronically and stored in Services for Sensitive Data (TSD), (https://www.uio.no/english/services/it/research/sensitive-data/about/index.html). Names of participants will be stored in separate files, only accessible by the project leader and data administrator. Deidentified data will be transferred to national and international collaborators through TSD. The teachers and the parents are informed about this process in their informed consent forms.

### 2.10. Participant remuneration

Schools participating in the study will not be compensated for the time used to implement the intervention and participate in the RCT. However, after the study has ended, the principal or school contact person will receive a small gift as an appreciation for their work and effort.

### 2.11. User involvement

During the development of the intervention, three focus group interviews involving 18 pupils were conducted with pupils from two secondary schools, to gain knowledge about their experiences with sexual and gendered harassment in school and how school personnel respond to harassment. (These schools were not a part of the current study). Two of the interviewed pupils have further contributed with feedback to the development of the pilot intervention that was tested in 2018 in order to assess pupils' and teachers' experiences with the intervention. One of these pupils and another youth have also contributed with feedback about the modification of the intervention which was later named “Stop Sexual Harassment” as well as the planning of the RCT study.

## 3. Method and analysis: Process evaluation

### 3.1. Study design

In this study, a process evaluation with focus group interviews will also be conducted. The study will thus utilise qualitative data to assess implementation quality and intervention fidelity.

### 3.2. Recruitment of participants

All principals in the intervention group were invited by e-mail or phone to participate in a process evaluation of the intervention. Three schools from wave 1 volunteered for focus group interviews. However, the interviews were cancelled due to national COVID-19 imposed regulations restricting pupils to meet between classes and a high number of pupils and teachers being absent from school. Online meetings were not considered, as participation would require individual rooms for participants at each class. It was decided to postpone the focus group interviews to wave 2. For wave 2, three schools will be invited to participate in the focus group interviews. At each school, there will be one interview with six pupils, and one interview with six teachers. The recruitment of teachers and pupils to focus group interviews will be conducted by the principals, with the instruction to balance the informant group with regard to gender and age. Prior to participation in the interviews, parents, pupils and teachers will be given information about the process study and asked to sign consent/assent forms.

